### Recruitment {15}

Acne vulgaris is a common condition. However, it is more common in the private sector than in public hospitals. Some centres such as Nantes have a one-day consultation devoted to acne. A feasibility study performed in each centre showed that between 8 and 15 patients per centre could be included per year, making these recruitment targets achievable.

## Assignment of interventions: allocation

### Sequence generation {16a} and concealment mechanisms {16b}

This balanced block randomization is computer-generated. Subjects are randomized into blocks as the allocation progresses, a block being a subgroup of predetermined size within which there is a random allocation of patients. The software SAS version 9.4 is used for randomization. The randomization will be centralized and stratified based on the following four groups of based on the type of contraception used by the participants:
Strata 1: implant, generation I and II OCs, progesterone intrauterine device or other kind of hormonal contraception (vaginal ring, patch, injection)Strata 2: copper intrauterine device (IUD) (hormone-free contraception)Strata 3: generation III and IV OCsStrata 4: no contraception (sterilization surgery or menopause)

### Implementation {16c}

The randomization key is known only to the biostatistician and data managers, to make it impossible for the investigator to assign a specific treatment. At the randomization visit (day 0) the investigator will check the inclusion and non-inclusion criteria, and then validate the randomization on the electronic case report form (eCRF). Drug prescriptions (blindspironolactone/doxycycline) will be made out for 2 months. In addition, a concomitant topical therapy, benzoyl peroxide 5%, will be given.

## Assignment of interventions in a double-blind method

### Who will be blinded {17a}

Our study is a randomized double-blind trial during the first 6 months (timeline for the primary objective), and an open tria during the last 6 months of follow up. The female patients will be randomized either to the acne routine care arm, i.e. cycline (doxycycline 100 mg/day for 3 months followed by a placebo for 3 months) or to the experimental drug arm (spironolactone 150 mg/day for 12 months).

The patients and the investigators and their teams will only be blinded to the treatment assigned during the first 6 months. As Karanicolas et al. pointed out in their article from 2010, their study should have been masked to the biostatisticians until analyses had been performed, to reduce the study bias [45].

Blinding will be removed for all patients after 6 months of evaluation - once the primary endpoint has been measured - whatever the result, to limit the constraints for the patients in the doxycycline arm. If blinding were maintained, patients in the doxycycline arm would have to take a placebo for up to 6 months in addition to the 3 months already taken. The objective of the last 6 months of follow up is to assess the maintenance of the efficacy of each treatment during this time.

### Procedure for unblinding if needed {17b}

The investigator should inform the Sponsor if unblinding is deemed to be necessary due to an emergency. Unblinding will be performed via the eCRF thanks to a detailed procedure that will be given to each site. Each decoding will be tracked and classified in the investigator’s management file and in the trial management file.

## Data collection and management

### Plans for the assessment and collection of outcomes - description of the parameters for evaluating efficacy {18a}

The first endpoint is the new validated score for adult female acne: the Adult Female Acne Scoring Tool (AFAST) [36]. The AFAST uses two independent scores: score 1 corresponding to GEA grading for acne on the face [34] and score 2 corresponding to the evaluation of the mandibular region. Scores are not added together. For each patient, AFAST score 1 (GEA) and AFAST score 2 should be assessed by the same evaluator at each visit.

The other score we will use is the ECLA. The ECLA chart for evaluation of acne has been developed by six dermatologists (in private and hospital practice) [35]. It is composed of 3 factors: factor 1 (F1) counts the acne lesions on the face, factor 2 (F2) counts the acne lesions on the trunk and factor 3 (F3) counts the scars. In this study, only factor F2 will be used. Factor F2 assesses the extensive character of acne lesions in five defined areas: cervical area (F2N), chest area (F2C), back area (F2B) and arm area (F2A) according to a qualitative scale where 0 = absent, 1 = poor, 2 = medium and 3 = significant. It is completed by counting the nodules present in each area.

With regard to the study questionnaires, we will use the EQ-5D and the CADI. The EQ-5D questionnaire, validated in France [46], will be given to the patient at each visit to measure their quality of life. The EQ-5D consists of a questionnaire and a visual analogue scale. The questionnaire focuses on 5 dimensions: mobility, personal autonomy, current activities, pain/discomfort and anxiety/depression. For each of these dimensions, three answers are possible (EQ-5D-3 L), thus allowing for 243 health states. The CADI is a disease-specific questionnaire measuring disability induced by acne [47]. It is a well-known acne disability measure and has been used in some studies to assess the burden of living with acne on a patient’s experience of disability [48, 49]. The questionnaire was developed as a multidimensional measure related to the impact of acne [50]. It is a 5-item scale: questions 1 and 2 address the psychological and social consequences of acne in general; question 3 is targeted at those with acne of the chest or back; question 4 enquires about the patient’s psychological state; and question 5 asks for the patient’s (subjective) assessment of their current acne severity. The response to each question is scored from 0 to 3. CADI is validated by our team in French [51].

Bacterial and parasitic samples will be collected from the nodulocystic and pustular skin of the participants at D0 and M4, using an Eswab to be delivered in an AMIES transport environment (1 ml). The analysis will be centralized at Nantes University hospital and performed by [name].

### Plan to promote participant retention and complete {18b}

The patient will be given a diary at the randomization visit, to note their health resource consumption, medical compliance, concomitant treatments and AEs. The visits will be arranged every 2 months up to M6, where the main objective is set. Empty blisters will be collected and counted at each visit. At each visit, the drugs prescribed will be for 2 months (blinded allocation of spironolactone/doxycycline and a placebo plus concomitant topical therapy). At visit M2 (2 months after randomization), the physician or a member of their team will have to be vigilant and tell the patient to carefully follow the chronological order of treatments. Two envelopes will be given to the patient, one for M3 (blinded allocation of spironolactone or doxycycline) and one for M4 (blinded allocation spironolactone or a placebo in place of doxycycline). As aforementioned, the guidelines stipulate that treatment with doxycycline should not exceed 3 months. For this reason, patients in the doxycycline arm will be given a placebo during month 4 and the following months [41–43].

### Data management {19}

An eCRF will be drawn up for each participant. The participant will be identified using the first letter of the family name, the first letter of the first name, the centre number and the inclusion number, supplemented by the month and year of birth. This code should be the only information featured in the eCRF, enabling a retrospective link with the patient.

The investigator will also encode the patient data on any documents that may be in their possession (imaging, biology test reports, etc.) and attached to the eCRF. At the end of the study, the CRF database and safety database will be reconciled. This reconciliation will be performed before database locking. Similarly, an annual reconciliation will be carried out when updating the Annual Safety Report (ASR).

### Confidentiality {27}

Each patient’s medical data will only be provided to the Sponsor or any person duly authorized by the Sponsor and, where applicable, to authorized health authorities, under conditions of confidentiality. The Sponsor and the supervisory authorities may request direct access to medical records for the purposes of verification of the procedures and/or data in respect of the clinical trial, within the limits authorized by legislation and regulations. The data compiled during the trial may be processed electronically in compliance with the French Data Protection Agency (CNIL) requirements. CNIL is an independent French administrative regulatory body whose mission is to ensure that data privacy legislation is applied to the collection, storage and use of personal data.

### Plans for the collection, laboratory evaluation and storage of biological specimens for genetic or molecular analysis in this trial/future use {33}

At the end of the study, participants’ biological samples (bacterial strains) will be kept in anticipation of further scientific benefit, but naturally the participant’s written consent will be obtained. The samples will be stored in the biocollection under the responsibility of [name]. This biocollection and its consent procedure have been registered under number DC-2011-1399 by the French Ethics Committee: CPP Ouest IV.

### Statistical methods

#### Statistical methods for primary and secondary outcomes {20a}

The primary efficacy variable is the percentage of success defined in “Background and rationale” (paragraph 2.1.2). The comparison between the two arms will be done using a Cochran–Mantel–Haenszel test checking for class of contraception (four strata). Modified intention to treat (ITTm) andlysis will be applied. That implies that to maintain the initial statistical power of the ITTm analysis, all randomized patients will be included in the final analysis, minus those who did not fulfil the inclusion criteria after randomization and those who never began their treatment.

All secondary objectives are expressed as a percentage or a status at a fixed time of follow up. General linear mixed models will be planned to take into account the repeated measurements collected on the same participant during their follow up. The Cox model with time-dependent covariates can also be used for secondary objectives for which a status is considered. Significance will be set at 5% in a bilateral situation.

For the cost-effectiveness analysis, 95% confidence intervals for differential (between arms) costs and QALYs and for the incremental cost-effectiveness ratio (ICER) will be estimated using the non-parametric bootstrap estimation procedure.

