### Eligibility criteria {10}

It is commonly acknowledged that acne affecting female patients under 20 years of age is considered to be “adolescent female acne”. Since this protocol concerns adult female acne, the recruited patients will be women aged at least 20 years. These patients will have acne vulgaris with at least 10 inflammatory lesions and no more than 3 nodules. The eligibility criteria are shown in Table 1.

**Table 1 Tab1:** Inclusion and non-inclusion criteria of the FASCE trial

Inclusion criteria	Non-inclusion criteria
• Female patient ≥ 20 years old	• Patient affected by active/progressive diseases, as infections including hidradenitis suppurativa, cancers or endocrine syndrome (e.g. polycystic ovary syndrome)*,* Addison’s disease)
• Patient with acne, with at least 10 inflammatory lesions and no more than 3 nodules (GEA score between 2 and 4)	• Patient affected by rosacea (folliculitis)
• Patient who already had one cycline course for her acne treatment with a 3-month* wash out or who never took any cyclines	• Patient with contra-indication to the use of one of the investigational products or auxiliary: ◦ Patient with intolerance or hypersensitivity to cyclines, spironolactone or to any ingredient present in associated benzoyl peroxide gel ◦ Patient with significant impairment of renal excretory function, acute or chronic renal failure, anuria ◦ Patient with life-threatening or very severe hepatic impairment. (grade III or IV)
• Patient having signed an informed consent	• Patient with hyperkalaemia or strongly requiring potassium-sparing diuretics (e.g. amiloride, canrenoate, eplerenone, triamterene) or treated continuously with ACE inhibitors, angiotensin II antagonist, NSAIDs, heparin and molecular-weight heparin, ciclosporin and tacrolimus, or treated with lithium
• Absence of use of oral antibiotics and zinc salts in the last 30 days	• Patient requiring topical isotretinoin or who stopped this drug less than 2 weeks ago
• Absence of use of topical antibiotics in the last 15 days	• Association with potassium salts except in the case of hypokalaemia
• Absence of use of systemic isotretinoin and antiandrogens in the last 6 months (but antiandrogens used as contraceptive are authorized)	• Patient previously treated with spironolactone
• Absence of microphysiotherapy in the last 15 days	• Pregnant woman or likely to become pregnant or nursing and refusing to use an effective contraceptive method

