### Outcomes {12}

The primary endpoint corresponding to the treatment efficacy is determined by the probability of success in each arm. In order to reduce the variability related to the fluctuation over time of the therapeutic response, we took the maximum value of this response. This maximum value appears between the fourth and sixth month of treatment. We could also have taken the average measured over 2 months, but clinically this is not interesting because the optimal time of efficacy is different between the two treatments This probability of success (or relapse) is defined by a decrease in both AFAST scores: (1) AFAST score 1 (corresponding to the GEA score): decrease of at least two grades compared to baseline or to grade 0 if the baseline was at 1, and (2) AFAST score 2 (mandibular score): decrease to grade 1 if baseline was > 1 or to grade 0 if the baseline was at 1.

AFAST score 1 (also called GEA) assesses the comedones (open and closed), the non-inflammatory lesions, the papules and pustules and the nodules. The stage is defined according to a global evaluation of severity of acne and ranges from grade 0 (no acne) to grade 5 (the worst situation). AFAST score 2 assesses acne on an area from the left and right mandibular zone to the upper edge of the trunk and ranges from grade 0 (no acne) to grade 3 (the worst situation).

For the secondary endpoints:
Safety/tolerance: reporting of the number and type of adverse events (AEs) and serious adverse events (SAEs) up to month 12 of follow up and abnormal values of ionogram (sodium, potassium, chlorine and calcium) at 0, 2, 4 and 9 months. First the percentage of AEs and SAEs will be calculated then they will be classified according to the organ affected.Efficacy: these outcomes correspond to the reporting of the:
Number of patients with AFAST score 1 (GEA) at 0 or 1, at M2, M4, M6, M9 and M12Number of patients with AFAST score 2 (mandibular) at 0 or 1, at M2, M4, M6, M9 and M12Number of patients with both AFAST scores 1 and 2 at 0 or 1, at M2, M4, M6, M9 and M12Number of inflammatory lesions of the face at D0 (baseline), M2, M4, M6, M9 and M12Number of retentional lesions of the face at D0, M2, M4, M6, M9 and M12Number of face lesions at D0, M2, M4, M6, M9 and M12Number of trunk lesions (factor F2 of ECLA) at D0, M2, M4, M6, M9 and M12Number of patients with relapses at M4 and M6

The definition of relapse is the same as the primary endpoint:

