### Sample size {14}

For sample size estimation purposes, the targeted difference in the percentage of success is 70% in the experimental arm compared with 50% success in the control arm, indicating a relative increase in success equal to 40%. Assuming a type I error rate of 5% and at least 80% statistical power, the sample size required is at least 91 subjects per group. To take into account the possibility of patients being lost to follow up, 10% (9 subjects) will be added to each group. Finally, approximately 200 subjects will be randomized to the two arms in a 1:1 ratio.

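### The primary test adjusts for contraception only; adding baseline GEA, which sets how far a woman must improve to succeed, would use precision the plan now forgoes

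*Protocol article*

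**What the plan says.** The section on statistical methods for primary and secondary outcomes {20a} of the Protocol article compares the two percentages of success by a CMH "test checking for class of contraception (four strata"). It adds: "Significance will be set at 5% in a bilateral situation". The test mirrors the allocation, which is described under sequence generation {16a}: "The randomization will be centralized and stratified based on the following four groups", all defined by contraception.

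Outcomes {12} defines success by two conditions that must both hold. For AFAST score 1 (GEA) it is a "decrease of at least two grades compared to baseline or to grade 0 if the baseline was at 1". For AFAST score 2 (mandibular) it is a fall to grade 1 from a higher baseline, or to 0 from 1. Table 1 under Eligibility criteria {10} admits GEA 2 to 4, so the clause about a baseline of 1 does not come into play for score 1.

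Sample size {14} states that "the targeted difference in the percentage of success is 70% in the experimental arm compared with 50% success in the control arm". It uses these overall rates with no covariate.

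**The concern.** The GEA target moves with the starting grade:

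| Baseline GEA | Grade needed for success |
|---|---|
| 2 | 0 (no acne) |
| 3 | 1 or less |
| 4 | 2 or less, a grade that would still meet the entry range |

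The AFAST score 2 condition also depends on its baseline: from 3 the fall must be two grades, from 2 or 1 only one.

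The background section justifies the contraception strata by the expected effect of contraception on acne. The same reasoning applies at least as well to the variable that enters the definition of success, and that variable is known at D0 for every woman because the endpoint cannot be scored without it. If success does vary with baseline GEA, leaving GEA out of both allocation and test lets chance differences in GEA mix between arms add noise to the risk difference. At stake is precision, not validity.

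**Working it through.** **1. The plan's own figure.** Inputs from Sample size {14}: 70% v 50%, and "Assuming a type I error rate of 5% and at least 80% statistical power". Two-sided, unpooled variance:

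n = (1.95996 + 0.84162)² × (0.7×0.3 + 0.5×0.5) / 0.2² = 7.8489 × 0.46 / 0.04 = 90.26, so 91 per group. This reproduces.

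With pooled variance under the null, z = (0.2√n − 1.96√(2×0.6×0.4)) / √0.46. At n = 100, z = (2 − 1.358)/0.678 = 0.947 and power is 82.8%. At n = 91 it is 79.1%. So about 200 women give the stated power at these rates without any covariate.

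**2. What adding GEA does to power.** The documents give neither the GEA mix nor success by grade, so these are assumptions: GEA 2/3/4 in 35/50/15% or equal thirds; contraception classes in 40/30/25/5%; the same odds ratio (OR) of success per baseline grade in both arms; overall rates held at 70% and 50%. Each scenario has 3,000 simulated trials of 200 women, with blocks of four within contraception strata. The statistic, without continuity correction, is

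X² = [Σ(a − n₁y/n)]² / Σ[n₁n₀y(n − y) / (n²(n − 1))], compared with 3.84,

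where, in each stratum, a is successes on spironolactone, y all successes, n₁ and n₀ the arm sizes and n their sum.

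| OR per grade | GEA mix | Power, contraception only | Power, contraception × GEA | Change (points) |
|---|---|---|---|---|
| 1 | 35/50/15 | 83.7% | 81.6% | −2.1 |
| 1 | thirds | 81.0% | 79.6% | −1.4 |
| 2 | 35/50/15 | 83.3% | 83.8% | +0.5 |
| 2 | thirds | 82.4% | 83.2% | +0.8 |
| 3 | 35/50/15 | 83.6% | 85.7% | +2.1 |
| 3 | thirds | 83.7% | 87.8% | +4.1 |
| 5 | 35/50/15 | 83.1% | 88.9% | +5.8 |
| 5 | thirds | 83.5% | 91.4% | +7.9 |

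Type I error was 4.3–5.6% for both tests. The simulation standard error is about √(0.05×0.95/3000) = 0.4 points, so both hold 5%.

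**3. Chance imbalance.** Let p be the success rate by grade. The part of the risk difference due to chance GEA imbalance has standard deviation √(Var(p) × 2/100) with 100 per arm. Assume a GEA mix of 40/45/15%, and apply the control gradient to both arms.

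- Success 32/59/72%: mean 0.5015; Var(p) = 0.4×0.0329 + 0.45×0.0078 + 0.15×0.0477 = 0.0239; 1.96 × √(0.0239×0.02) = 0.043, about ±4 points.
- Success 20/65/84%: mean 0.4985; Var(p) = 0.4×0.0891 + 0.45×0.0230 + 0.15×0.1166 = 0.0635; 1.96 × √(0.0635×0.02) = 0.070, about ±7 points.

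The target difference is 20 points. The second gradient is steep: the odds from GEA 2 to GEA 3 rise by (0.65/0.35)/(0.20/0.80) = 7.4.

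**4. Sparse cells.** Four contraception classes × three GEA grades make 12 cells. With the assumed mix, the class without contraception at GEA 4 would hold 200 × 0.05 × 0.15 = 1.5 women. A cell with one arm only contributes nothing to the CMH test. The loss at OR 1 in the table includes this cost.

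**The case against.** **The planned test is sound.** It stratifies on the factor used in randomization. Omitting a prognostic covariate does not bias a randomized comparison, and the nominal alpha already allows for chance imbalance. The stated power is reached without GEA. All of this stands, so a reader who infers a power shortfall or a biased test goes further than the documents allow.

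**The gradient is assumed.** Success also needs the mandibular condition, and missing data, loss to follow-up and unacceptable toxicity count as failures; each may weaken the link with baseline GEA. Severe acne may also respond less, which would offset the easier target. This stands too. Adjustment gains precision whichever way the gradient runs, but if the two effects cancel it costs 1–2 points.

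**The analysis plan is not shown.** It may hold adjusted supportive analyses. But the article itself fixes the primary test and its only stratifier, and the point concerns that choice.

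**A stronger reading: prior cycline use handicaps the comparator.** Table 1 admits a "Patient who already had one cycline course for her acne treatment", after washout, and bars a "Patient previously treated with spironolactone". One might infer that doxycycline is re-treating earlier failures, so that a win would say little about first-line use. The documents do not support this. Table 1 does not say that the earlier course failed. The background remarks on resistance and on reported antibiotic failures give no re-treatment response rate. The objective concerns adult female acne, not cycline-naive women.

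If real, the effect would be effect modification, balanced in expectation by randomization. Adding prior use as a stratum does not help: with half the women pretreated and control success of 60% v 40%, or 55% v 45%, power goes from 82.5% to 81.8%, or from 81.5% to 80.8%. An interaction test would be weak. Suppose effects of 27 points in 120 pretreated women (70% v 43%) and 10 points in 80 naive women (70% v 60%). The standard error is √(0.21/60 + 0.2451/60 + 0.21/40 + 0.24/40) = 0.137, z = 0.17/0.137 = 1.24, and power is about 24%.

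**Conclusion.** The point holds as a recommended refinement, not as an error. The primary analysis leaves out a baseline variable that is written into the success rule and already collected. The size is a change in power of about −2 to +4 points for odds ratios of 1 to 3 per grade and +6 to +8 points at an odds ratio of 5. Removing chance GEA imbalance takes out a component of about ±4 to ±7 points under the two gradients above. These figures rest on assumed GEA and contraception mixes and gradients, and on 70% and 50% being the success rates in the analysed set. The documents cannot narrow the range. No conclusion about bias, inflated type I error, insufficient sample size or a handicapped comparator follows.

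**What to change.** Add baseline GEA (2/3/4) to the primary analysis in one of two ways:

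- CMH strata of contraception × baseline GEA, with a rule set in advance for merging sparse cells; or
- logistic regression on arm, contraception and baseline GEA (optionally baseline AFAST score 2), reporting a standardised risk difference so that the result stays on the scale of the 70% v 50% target.

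Keep the contraception-only CMH test as a sensitivity analysis. Date the change and make it before anyone sees outcomes by arm. This matters because each woman is unblinded after month 6, and the randomization key is known to the biostatistician and data managers.

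The cost is a sentence or two in the analysis section, some sparse strata, and 1–2 points of power if GEA is not prognostic. No new data or patients are needed. At most, an estimate by prior cycline course could be reported as exploratory.

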## Interventions

### Explanation for the choice of comparators {6b}

As already stated, although acne is not an infectious disease, oral antibiotics have remained a mainstay of treatment over the last 40 years. The anti-inflammatory properties of oral antibiotics, particularly cyclines, are effective in treating inflammatory acne [39, 40].

All the guidelines - French [41], European [42] and American [43] - recommend cycline for first-line treatment but limited to a treatment period of 3 months to minimize the development of bacterial resistance. This is why the treatment duration of the comparator arm we chose is doxycycline 100 mg/day for 3 months. The guidelines specify also that monotherapy with a systemic antibiotic is not recommended. Concomitant topical therapy with, for example, benzoyl peroxide should be used with systemic antibiotics and for maintenance after completion of systemic antibiotic therapy. Patients in the two study arms will receive this topical therapy.

The primary objective is the efficacy of doxycycline or spironolactone seen at M4 and/or M6. To avoid results bias and because our experience shows that maximum efficacy is seen for cycline between M4 and M6, the best clinical response between M4 and M6 will be chosen for the primary endpoint.

The response of acne to spironolactone may not be optimal after only 3 months of treatment [22]. A retrospective trial reported by Burcke and Cunliffe showed an average reduction in acne that was optimal at month 6 [24].

In conclusion, in order not to bias the study in either direction, regarding the primary objective, the efficacy of the two treatments will be measured at 4 and 6 months in each arm and the best results in the two arms will be compared (Fig. 1). At the end of the M6 visit, after the clinical evaluation, all the data will be accessible and open to the patient and the investigator. Patients with complete or partial remission will continue the trial. Other patients will drop out of the trial and be treated by the investigators according to their usual practice. The same approach will be used at the M9 visit: relapse patients will drop out of the trial and will be treated by the investigators according to their usual practice.

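### The optional Cox model for the secondary status endpoints compares hazards, not status at the named visits, and can lose much of its power if spironolactone acts later

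*Protocol article*

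**What the plan says.** Statistical methods {20a} fixes the scale of the secondary objectives: "All secondary objectives are expressed as a percentage or a status at a fixed time of follow up". It then names a main approach, "General linear mixed models will be planned to take into account the repeated measurements collected on the same participant during their follow up", and adds a second one: "The Cox model with time-dependent covariates can also be used for secondary objectives for which a status is considered". It does not say what the event is, whether only the first occurrence counts, or which covariates vary over time. The significance rule is "Significance will be set at 5% in a bilateral situation".

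Outcomes {12} counts women with GEA at 0 or 1, mandibular score at 0 or 1, and both at 0 or 1, separately at M2, M4, M6, M9 and M12. Relapse is counted at M4 and M6, so response is treated as something that can be lost.

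On timing, Outcomes {12} rejects averaging over visits because "clinically this is not interesting because the optimal time of efficacy is different between the two treatments". The comparator section {6b} adds: "The response of acne to spironolactone may not be optimal after only 3 months of treatment". The same section places the best cycline effect between M4 and M6.

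**The concern.** The stated question is whether the arms differ in the share of women in a given status at a named visit. A Cox model asks whether the rate of reaching an event differs over follow-up. The two answers agree when the arms have the same time pattern and nobody loses the status. The protocol gives reasons to expect neither: different timing by arm, relapse as an endpoint, and a comparator that becomes placebo after month 3 while spironolactone continues.

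If the event is first response, a woman who responds at M2 and has lost the response by M6 still counts as an event, and early responses weigh heavily. A later but larger spironolactone response could then be shown at M6 by one permitted analysis and not by the other, for the same endpoint.

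**Working it through.** **Inputs.** From Sample size {14}: "the targeted difference in the percentage of success is 70% in the experimental arm compared with 50% success in the control arm", with "at least 80% statistical power, the sample size required is at least 91 subjects per group", and about 200 women randomised 1:1, so 100 per arm. These rates belong to the primary endpoint and are borrowed here as M6 status rates. The documents give no rates by visit and none for loss of response, so all visit patterns below are assumptions.

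**Step 1: the plan's own figure.** With unpooled variance, n = (z₀.₉₇₅ + z₀.₈₀)² × [p₁(1−p₁) + p₂(1−p₂)] / (p₂−p₁)² = (1.960 + 0.842)² × (0.25 + 0.21) / 0.04 = 90.3, so 91 per arm, as stated (93 with pooled variance). At 100 per arm, the power of the two-proportion test is Φ{[0.20 × 10 − 1.96 × √(2 × 0.6 × 0.4)] / √0.46} = Φ(0.947) = 82.8%.

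**Step 2: first response without and with loss.** Each arm was given a cumulative percentage of women who had ever responded by M2/M4/M6. Status at M6 was held at 50% (doxycycline) v 70% (spironolactone) in every row. A Cox model with treatment only was fitted to first response (two-sided 5%, 100 per arm, 2,000 runs). Favours S and Favours D are the percentages of runs in which Cox is significant for spironolactone or doxycycline.

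| Scenario | Doxycycline | Spironolactone | Cox HR | Favours S | Favours D | M6 status test |
|---|---|---|---|---|---|---|
| No lag, no loss | 20/38/50 | 32/56/70 | 1.73 | 84% | 0% | 82% |
| Mild lag, no loss | 22/40/50 | 18/48/70 | 1.54 | 63% | 0% | 82% |
| Strong lag, no loss | 30/45/50 | 10/40/70 | 1.33 | 33% | 0% | 83% |
| Stronger lag, no loss | 40/48/50 | 10/30/70 | 1.23 | 22% | 0.1% | 83% |
| No lag, doxycycline loses 10 points | 25/48/60 | 30/55/70 | 1.29 | 29% | 0% | 83% |
| Strong lag, doxycycline loses 10 points | 35/55/60 | 10/40/70 | 0.98 | 2% | 4% | 83% |
| Strong lag, doxycycline loses 20 points | 40/62/70 | 15/45/70 | 0.78 | 0% | 32% | 85% |
| Stronger lag, doxycycline loses 20 points | 50/68/70 | 10/35/70 | 0.67 | 0% | 65% | 84% |

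**Step 3: status that comes and goes in both arms.** Status at each visit was drawn from a latent Gaussian AR(1) process with correlation 0.7 to 0.9. The log-rank test of first response (the Cox score test with treatment only) was compared with the M6 status test over 4,000 runs.

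- Doxycycline 25/45/50% v spironolactone 15/50/70% (10 points behind at M2): Cox power for spironolactone 15–29%.
- Doxycycline 30/50/50% v spironolactone 15/45/70% (15 points behind at M2): 2–9%.
- Only 3 points behind at M2: 24–40%.
- M6 status test: about 83% throughout. Significant inferiority of spironolactone on Cox: under 3% in both of the first two patterns.

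**Step 4: what a time-dependent treatment term would do.** Take the strong-lag, no-loss row. The visit hazard is h = (newly responded) / (not yet responded), and the hazard ratio is ln(1−h_S) / ln(1−h_D).

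- M2: h_D = 0.30, h_S = 0.10, ratio 0.30.
- M4: h_D = 0.15/0.70 = 0.214, h_S = 0.30/0.90 = 0.333, ratio 1.68.
- M6: h_D = 0.05/0.55 = 0.091, h_S = 0.30/0.60 = 0.500, ratio 7.27.

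The hazards cross, so such a term would show the later benefit. None of the three ratios is the 20-point difference in status at M6.

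**The case against.** Cox is optional: mixed models are what is planned. The article is condensed, and an analysis plan that is not shown may define the event and the covariates. That absence is not counted here. What stands is narrower: the article itself names, for endpoints it defines as status at a visit, a method that does not estimate that quantity.

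Four stronger readings are tempting, and the documents do not support them.

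- **A better spironolactone would read as inferior.** This was rare (under 3%) when status fluctuated in both arms. It became common only when an M2 deficit of 25 points or more combined with marked loss of doxycycline response.
- **Cox has an inflated false-positive rate.** With equal status at M6, Cox can favour doxycycline well above 5% of the time, but only because doxycycline was assumed truly ahead at M2 and M4. Those are also named visits, so the model would be finding a real earlier difference.
- **Cox must miss the benefit.** The simulations used treatment only, whereas the text allows time-dependent covariates. In the Step 3 patterns with a 10–15 point deficit, a treatment contrast for the M6 interval favoured spironolactone in 62–96% of runs. That softens the loss of power but does not restore the stated estimand.
- **The covariates would adjust away the drug effect.** That is a risk of post-randomisation covariates in general, but the text names none.

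First response is itself an interpretation of an undefined event. The size, and even the presence, of an early deficit is unknown: {6b} puts the best cycline effect at M4 to M6, and Intervention description {11a} cites spironolactone response over roughly 3 months. Relapse is a status objective for which a time-to-event analysis would be natural if it were defined as one.

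**Conclusion.** The point holds as a mismatch between objective and method. The Cox option does not estimate the fixed-visit difference in status, and under the timing that the protocol itself expects it can lose much of the power to show a later spironolactone advantage. With 70% v 50% at M6 and 100 per arm, power is about 83% for the fixed-visit test. For a treatment-only first-response Cox model it runs from about 84% (no lag) to 2–30% (10–15 points behind at M2). The direction follows from the definitions. The size rests on assumed visit rates, a first-event reading and a model without time-dependent terms. Only secondary endpoints are affected; the primary Cochran–Mantel–Haenszel (CMH) comparison is untouched.

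**What to change.** - For the status-at-visit endpoints, replace the Cox sentence with one named fixed-visit analysis. This can be a CMH test at each visit stratified by the four contraception classes, or the arm-by-visit contrast of a mixed model for binary data adjusted for that class. Use no post-randomisation covariates.
- At M9 and M12, do not restrict the comparison to women still in the trial. Under {6b} and {11a} non-responders leave at M6, and under {6b} relapsers leave at M9, so those remaining are selected on outcome. Count the women who left for these reasons as not in the status. This needs an exception to the rule in {20c} that drops women with missing data from the clinical secondary analyses.
- If a time-to-event summary is wanted, define it as a separate exploratory endpoint, such as time to first remission or to relapse, with its event and time origin stated.

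The cost is a few lines of text and no new data or visits. An optional time-to-event summary is lost for these endpoints. The M9 and M12 results would describe status held without withdrawal, so a woman who clears on other treatment after leaving counts as not in the status.
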